### Outcome assessment

At six months post-intervention (approximately 24 weeks from the time of randomisation), control and intervention participants will be invited back to the diabetes clinic in the same staggered manner as they were recruited. At this time point, HbA1c, blood pressure, cholesterol and body-mass index will be taken again and recorded. The baseline questionnaires will also be re-administered. In addition, a record will be kept of participation rates throughout the intervention and reasons for non-participation where possible. Participants will again be given a questionnaire pack containing the family member measures, and asked to ensure that their nominated family member completes the questionnaires and returns them to the researcher by post.

### Randomisation

After consent and baseline data have been collected from the first 40 patients, they will be randomized into intervention and control groups by using computer generated random number tables. The main investigators will not be involved in the randomisation procedure, which will be carried out by an independent expert. The use of block randomisation means that the intervention can be delivered in a staggered manner, with some participants beginning the intervention while further recruitment continues. When the next 40 patients are recruited, they will then be randomly allocated to intervention or control groups, and so on, until 122 patients are included in the trial. Due to the psychological nature of the intervention, it is not possible for the investigator delivering the intervention to be blind to participants' treatment allocation group.

### Intervention

The intervention is a complex psychological intervention designed to change the illness perceptions of patients with type 2 diabetes and their family members. The starting point for the intervention is the illness perceptions models of diabetes held by the patient and the family member and the degree of similarity between these models. The intervention is based upon clarifying the five illness perception dimensions of both the patient and the family member in relation to diabetes, examining how they influence self-management behaviours, and developing personalized action plans. The intervention will be tailored to each individual patient and family member; thus, the exact content of each session will depend upon the individual illness perceptions of the patient and family member, and the degree of congruency between these perceptions. In essence, the intervention is designed to change any inaccurate and/or negative illness perceptions which the patient or family member may have, and improve the degree of congruence of patient and family member perceptions, in a positive direction. A sample case study is presented in Table 1 to illustrate how the intervention might work (Table 1: sample case study for intervention). A more detailed description of the intervention can be found in the intervention manual (see additional file 1)

**Table 1 T1:** Sample case study for intervention

The intervention that is the focus of this study is relatively brief, in view of recent research suggesting that briefer psychosocial interventions can be more easily integrated into routine care. Due to the brief nature of the intervention and its emphasis on behaviour change, techniques from brief motivational interviewing [54] will be used to deliver the intervention. These techniques have been successfully used in other brief interventions of this type [55,56]. The intervention will consist of three sessions delivered on a weekly basis, the first two of which will take place in the patient's home with their family member, and the last one of which consists of a phone call to the person with diabetes. Sessions will be delivered by a health psychologist who is trained in motivational interviewing techniques. Each session will last approximately 40 minutes.

### Sample size and rate of recruitment

Taking HbA1c and Diabetes Well-being as primary outcomes, a total sample size of 76 and 86 respectively, were calculated. This was using 80% power to detect a significant *absolute *change of 0.9% in glycaemic control (this absolute change has been related to clinical outcomes in the UK prospective diabetes study, [3] and of 3 points in the Diabetes Well-being Scale-12. These calculations also allow for an anticipated "Hawthorn effect" relating to an improvement of 20% for those in the control group, by virtue of the fact that they are participating in the research. Taking the larger number of86 participants (43 inintervention and 43 in control group), a final total number of 122 participants (61 in each group) is needed to ensure at least a 70% final response rate is met. Previous research in the diabetes clinic [33] has shown that it is possible for one researcher to see approximately two to three eligible patients per clinic. Thus, it is estimated that it will take approximately 8–10 weeks to recruit the required 40 participants for the first block for randomisation.

### Qualitative component

Participants with type 2 diabetes (in the intervention group only) will be asked to complete a brief diary on a weekly basis for the first six weeks and every second week for the remaining eighteen weeks. Diaries will be structured to allow for the examination of the intervention and the process of change over time. In order to maximize compliance to filling in the diary, weekly/fornightly text messages will be sent to remind participants to fill in their diary. A computer program will be used to send text messages to a large number of mobile phones at regular intervals.

### Quality assurance

The process evaluation component of this RCT will run alongside data collection and intervention delivery. The use of both qualitative and quantitative data provides the strongest evidence for process evaluation [57,58]. Therefore, qualitative and quantitative process evaluation data will be collected in this study, focusing on aspects of intervention implementation, participant experience of receipt of the intervention, and the influence of contextual/setting factors. See Table 2 for an outline of the process evaluation questions and data collection tools (Table 2: process evaluation components).

**Table 2 T2:** Process evaluation components

Process Evaluation Questions	Data Collection Tool	Source	Trial Stage
***Implementation*** **Was the intervention properly delivered?** **Treatment fidelity to different components.** **Monitor dose/participant exposure to intervention components**	1.10% of sessions randomly selected to be taped and analysed by independent expert in illness perceptions and motivational interviewing. Tapes analysed qualitatively and quantitatively using MI & IP checklists.	Randomly selected sub-sample of intervention participant's.	Collecting during intervention delivery. Analysed post-intervention

***Receipt*** **1.Participants views of the intervention and partaking in the RCT.**	1.Open-ended questionnaires for all participants in control and intervention groups	1. All participants	1. Collected at follow-up data collection
**2.Appropriateness of use of intervention and techniques for type 2 diabetes**	2. Focus groups with sub-sample of intervention participants	2. Sub-sample of intervention participant's.	2. Collection post-follow-up

***Contextual factors*** **What was the effect of various setting/contextual factors. e.g. interruptions during session, family dynamic, mood, etc.**	Structured field notes questionnaire (e.g. how long each session, where in home delivered, interruptions, dynamic, etc)	Interventionist	Collecting during intervention delivery. Analysed post-intervention
**Sub-groups variations (e.g. family member involved)**	Interventionist observations – field diary		

### Analysis

#### Quantitative analysis

SPSS Version 13.01 for Windows will be used in the analysis. Differences in biomedical, psychosocial and illness-specific outcomes between the intervention and control group will be analyzed for the two time-points (baseline and 6 months post- intervention). Further statistical analysis will be based on repeated measures analysis of variance. Statistical significance will be taken at the 5% level for primary outcomes, and at 1% level for secondary outcomes.

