### Screening eligibility

Potential participants will be recruited from two diabetes specialist clinics at the AMNCH Hospital in Tallaght in Dublin. All type 2 patients over 18 years, with at least two of their last three HbA1c readings of 8.0% or greater (eligible participants), will be identified through the auditing facility of the "Diamond" computer database (n~ 3560 type 2). Prior to each clinic a list of eligible patients attending the clinic will be generated by the Diamond database, who will subsequently be asked to participate in the study (see Figure 3: Flowchart of RCT).

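### HbA1c is compared on baseline and six-month values only; adjusting for baseline and for the screening readings already on file would cheaply narrow its confidence interval

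*Protocol article*

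**What the plan says.** - **Primary outcome.** Sample size and rate of recruitment: "Taking HbA1c and Diabetes Well-being as primary outcomes", with evaluable totals of 76 and 86 respectively. The larger figure, allowing for a 70% response rate, leads to 122 recruited.
- **Analysis.** Quantitative analysis: "Differences in biomedical, psychosocial and illness-specific outcomes between the intervention and control group will be analyzed for the two time-points", which are baseline and six months after the intervention. The next sentence bases further analysis on repeated measures analysis of variance. "Statistical significance will be taken at the 5% level for primary outcomes".
- **Readings already held.** Screening eligibility: patients "with at least two of their last three HbA1c readings of 8.0% or greater (eligible participants), will be identified through the auditing facility" of the clinic's computer database, with a list drawn up before each clinic.
- **Separate baseline.** Baseline assessment: a further HbA1c is taken at the recruitment appointment, so the three screening readings come before it and are distinct from it.

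**The concern.** A single HbA1c reading is an imperfect measure of a patient's usual level. The trial recognises this in its eligibility rule, which requires two high readings out of three to establish persistently poor control. The stated analysis of a primary outcome then works from one pre-treatment value, and enters it through a change score, which gives it a fixed weight of one instead of a weight estimated from the data.

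Two sources of precision are left unused: regression on the recruitment-visit value, and the earlier readings on file. All of these values precede randomisation, so pre-specified adjustment for them does not bias the comparison. What is at stake is the width of the HbA1c confidence interval. The validity of the comparison is not in question.

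**Working it through.** **1. The plan's own figures.** The HbA1c calculation rests on "This was using 80% power to detect a significant" absolute "change of 0.9% in glycaemic control". The article gives no SD, so 76 cannot be reproduced independently. At two-sided 5% (sidedness assumed), 38 per arm is what a difference of 0.9 requires if the SD is 1.4. The article also mentions a 20% control-group improvement; if that cut the difference to 0.72, the implied SD would be 1.12. For the recruited total, 86/0.7 = 122.9, against the stated 122.

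**2. HbA1c power at 86 completers.** If 76 give 80%, the standardised signal at 76 is 1.96 + 0.842 = 2.802. At 86 it is 2.802 × √(86/76) = 2.981. Power is Φ(2.981 − 1.96) = Φ(1.02), about 85%. The exact calculation with SD 1.4 and 43 per arm gives 84.6%.

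**3. Variance formulas.** Assume a common variance σ² and correlation r between any two readings, before any selection:
- change score: 2σ²(1 − r)
- ANCOVA on one baseline: σ²(1 − r²)
- ANCOVA on baseline and the mean of three earlier readings: σ²[1 − 4r²/(1 + 3r)]

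The last divided by the first simplifies to (1 + 4r)/[2(1 + 3r)]. This is 3/5 = 0.60 at r = 0.5 and 4.2/6.8 = 0.62 at r = 0.8. The last divided by the second is 0.60/0.75 = 0.80 at r = 0.5.

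**4. Applying the eligibility rule.** Selecting patients on the screening readings restricts their range and reduces what they can add. I therefore simulated five normal readings per patient (three screening, recruitment, six months), kept those with at least two of the first three at 8.0% or over, and computed residual variances. Assumptions: clinic mean 7.7% and SD 1.5; means of 7.5 and 8.0 with SD 1.4-1.5 change little. The correlations are also assumed. In the fading structure, the correlation between adjacent readings is r and is multiplied by 0.88 for each further interval.

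| Structure | r | Baseline ANCOVA / change score | Adding history / baseline ANCOVA | Both covariates / change score |
|---|---|---|---|---|
| Equal | 0.5 | 0.67 | 0.89 | 0.60 |
| Equal | 0.7 | 0.75 | 0.82 | 0.61 |
| Equal | 0.8 | 0.81 | 0.77 | 0.62 |
| Fading | 0.5 | 0.72 | 0.96 | 0.69 |
| Fading | 0.7 | 0.83 | 0.97 | 0.80 |
| Fading | 0.8 | 0.90 | 0.99 | 0.89 |
| AR(1) | 0.5 | 0.76 | 1.00 | 0.76 |
| AR(1) | 0.7 | 0.88 | 1.00 | 0.88 |
| AR(1) | 0.8 | 0.93 | 1.00 | 0.93 |

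Across the other means and SDs, the lowest history ratio under equal correlation is 0.76.

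**5. In terms of interval width.** Width scales with the square root of variance: √0.60 = 0.77 and √0.93 = 0.96. The two-covariate model narrows the HbA1c interval by about 4% to 23% against the change score. The history's own share runs from nothing to about 13% (√0.76 = 0.87).

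**The case against.** The strongest reply is that nothing here is wrong. Comparing randomised arms on baseline and six-month values is valid, and covariate lists are commonly left to an analysis plan that is not shown. That the method is valid stands in full. The appeal to an unseen plan stands only in part: the article does fix a model and its time points, and the point concerns that stated choice. A separate plan may still add covariates.

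A second reply is that the gain from the history cannot be established from the document. This also stands. The article gives no SD, no correlation and no timing for the earlier readings. If the recruitment value carries everything that the earlier ones do, as under AR(1), they add nothing. The larger figures require a reading from several visits back to predict the six-month value as well as the recruitment reading does.

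Three stronger readings are tempting, and the documents support none of them:
- **That HbA1c is underpowered, or that the history would lift it from 80% at 86 completers.** The 86 is the well-being requirement. HbA1c needs 76 and starts at about 85%.
- **That the trial could be smaller.** Well-being sets the 122, and HbA1c history cannot reduce it.
- **That the screening readings account for the whole gain.** Under AR(1) all of it comes from baseline adjustment, and under fading correlation nearly all of it does. Only under equal correlation is the history's share substantial.

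**Conclusion.** The point holds as a cheap, optional gain in precision on a primary outcome. The stated two-time-point analysis is sound but, in every scenario examined, less efficient than an ANCOVA on data that the trial already holds. With assumed correlations of 0.5-0.8, the two-covariate model has about 0.60-0.93 of the change-score variance. The history's contribution beyond baseline is 0% (AR(1)), 1-4% (fading) or about 11-24% (equal correlation). These ranges depend on the assumed correlations, normal readings and the assumed clinic mean and SD; the article supplies none of them. The benefit is a narrower HbA1c interval at the same sample size. No conclusion about bias, inadequate power or the recruitment target follows.

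**What to change.** In Quantitative analysis, state that six-month HbA1c will be compared between arms by ANCOVA, with the recruitment-visit HbA1c as a covariate and the mean of the last three pre-recruitment readings (the database values used for eligibility) as a second. Both should be specified before outcome data are seen. If only one change is made, the baseline covariate is the safer choice: it improves on the change score in every scenario and needs no extra data.

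The cost is one sentence, one field exported from a database already queried, and one degree of freedom for the historical mean. It needs no further patient contact and no change to the sample size.

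### With one baseline and one follow-up, repeated measures ANOVA is a valid but generally less efficient choice than baseline-adjusted ANCOVA, and the treatment-effect term is not named

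*Protocol article*

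**What the plan says.** The Quantitative analysis section of the protocol article fixes the data structure: "Differences in biomedical, psychosocial and illness-specific outcomes between the intervention and control group will be analyzed for the two time-points", these being baseline and six months post-intervention. It then names the model: "Further statistical analysis will be based on repeated measures analysis of variance". It mentions no baseline covariate and does not say which model term estimates the treatment effect. On significance it says: "Statistical significance will be taken at the 5% level for primary outcomes, and at 1% level for secondary outcomes".

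The Randomisation section places baseline before allocation: "After consent and baseline data have been collected from the first 40 patients, they will be randomized into intervention and control groups". Further batches follow in the same way: "When the next 40 patients are recruited, they will then be randomly allocated to intervention or control groups".

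The sample size section takes HbA1c and well-being as primary outcomes, with 80% power for a 0.9% absolute change in HbA1c and 3 points in well-being. It needs 76 and 86 patients in total respectively, and takes the larger figure, 43 per group. It gives no SD and no correlation between baseline and follow-up.

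**The concern.** Because baseline precedes randomisation, it cannot carry a treatment effect, yet a two-time-point repeated measures ANOVA treats it as one of the two responses. Two things follow.

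- **Efficiency.** The group-by-time test compares mean change between arms. It subtracts the whole baseline value, whereas ANCOVA subtracts the fraction that the data support. Unless the slope of follow-up on baseline is close to 1, the change score carries avoidable noise.
- **Ambiguity.** The same model also produces a between-group main effect. This averages a true zero at baseline with the difference at follow-up, so it estimates half the treatment effect. The article does not say which term is the trial's result.

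With about 43 analysed per arm there may be little power to spare, and the more precise analysis uses data the trial already collects.

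**Working it through.** **Inputs from the article:** 76 and 86 analysed in total for HbA1c and well-being, 43 per arm, 80% power, 5% level, effects of 0.9% and 3 points, 70% response.

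**Assumed:** a two-sided test, equal variances at both times, and a correlation r of 0.3, 0.5 or 0.7.

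**The plan's own figures.** 86/0.70 = 122.9, against 122 stated, which agrees to within one patient. The totals of 76 and 86 cannot be reproduced without SDs, so I solved backwards with SD = δ√(n/2)/(1.960 + 0.842):

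- Well-being: 3 × √21.5 / 2.802 = 4.97 points, a standardised effect of 0.604 (0.611 with the t distribution).
- HbA1c: 0.9 × √19 / 2.802 = 1.40 percentage points, a standardised effect of 0.643.

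Taking the 20% control-group improvement off the effect (2.4 points, 0.72%) lowers the back-solved SD in proportion (3.97, 1.12). The standardised effect, and hence the power figures below, do not change.

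**Variances relative to one six-month measurement:**

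- change score: 2(1 − r)
- ANCOVA: 1 − r²
- ratio of ANCOVA to change score: (1 + r)/2
- group main effect: (1 + r)/2, with half the effect

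**If the 80% refers to six-month values** (well-being, 43 per arm), power = Φ(2.802/√v − 1.960), where v is the relative variance. The number per arm for 80% power is 43 × v, rounded up.

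| r | v, change | v, ANCOVA | ratio | power, change | power, ANCOVA | n per arm, change | n per arm, ANCOVA |
|---|---|---|---|---|---|---|---|
| 0.3 | 1.40 | 0.91 | 0.65 | 65.8% | 83.6% | 61 | 40 |
| 0.5 | 1.00 | 0.75 | 0.75 | 80.0% | 89.9% | 43 | 33 |
| 0.7 | 0.60 | 0.51 | 0.85 | 95.1% | 97.5% | 26 | 22 |

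Example at r = 0.3: 2.802/√1.40 − 1.960 = 0.408, and Φ(0.408) = 65.8%. The 61 per arm needed there is the whole randomised arm, which leaves nothing for the planned 30% non-response.

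**If the 80% refers to change scores**, ANCOVA power = Φ(2.802/√((1+r)/2) − 1.960) = 93.5%, 89.9% and 86.0% at r = 0.3, 0.5 and 0.7.

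**If the group main effect were read as the result**, 3 points would be estimated as 1.5. Power = Φ(2.802/(2√((1+r)/2)) − 1.960) = 41%, 37% and 33% at r = 0.3, 0.5 and 0.7. For HbA1c, 0.9 would be estimated as 0.45. The factor 2.802 becomes 2.802 × √(43/38) = 2.980 because only 38 per arm are needed for 80%, which gives about 41% at r = 0.5.

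**Checks on the comparison.** In 20,000 simulated trials with 43 per arm, a true effect of 0.600 and r = 0.5, the mean estimate was 0.602 for both change score and ANCOVA, with a variance ratio of 0.758. When the slope is 1 (for example r = 0.8 with the follow-up SD 1.25 times the baseline SD), the large-sample variances are identical at 0.5625. At r = 0.98 the simulated ratio was 1.002, very slightly in favour of the change score.

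**The case against.** The strongest reply is that the planned analysis is sound on its ordinary reading. The interaction is the usual treatment test in a pre/post design, and the sample size section is framed as an absolute change, which fits it. An article condenses its analysis plan, the word 'Further' suggests more is planned, and the name of the reported term or a covariate list may sit in a fuller document. If the 80% was calculated for change scores, the trial has its stated power and ANCOVA is a bonus. If it was calculated for six-month values, the change score still reaches 80% from r = 0.5 upward.

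Most of this stands, and it rules out several stronger readings that a reader might infer:

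- *That the planned test is biased.* The interaction estimate is unbiased under randomisation. Halving arises only if the main effect is read as the result, which the article does not say will happen.
- *That ANCOVA is always more precise.* The two tie at a slope of 1, and in small samples near that point ANCOVA can be marginally worse.
- *That selecting patients on past high HbA1c distorts the comparison.* Selection applies to both arms alike. Only chance baseline imbalance matters, and the variance ratio already counts it.
- *That a significance test at baseline is planned.* Analysing differences for two time points can equally mean comparing change or describing each point.
- *That ignoring the batches of 40 is a material fault.* Its cost cannot be quantified from the article and is probably small.

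What the reply does not remove is that the article itself names the model and the two time points, and that a generally more efficient analysis of the same data is available.

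**Conclusion.** The point holds as an efficiency improvement with an ambiguity to clear up. It does not show an invalid analysis. The change-score test implied by the plan is unbiased, and the ANCOVA variance is about 65% to 85% of its variance for r between 0.3 and 0.7. In power at 43 per arm, the gain is about 18, 10 and 2 percentage points at r = 0.3, 0.5 and 0.7 if the stated 80% refers to six-month values. It is about 13.5, 10 and 6 points if the 80% refers to change scores. The gain shrinks towards nothing as the slope approaches 1.

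The algebra is exact in large samples under equal variances. The power figures rest on SDs back-solved from the stated totals, a two-sided test, and assumed correlations. It would go too far to say that the choice decides whether a real effect is found: at high correlation both tests are well powered. The low power of the main effect is conditional on a reading the article neither states nor excludes.

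**What to change.** Replace the repeated measures sentence with the following:

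> Each continuous outcome at 6 months will be compared between groups as randomised by ANCOVA with the baseline value of that outcome as covariate; the adjusted mean difference with 95% CI is the treatment effect.

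Summarise baseline by group descriptively. If repeated measures ANOVA is kept, the least that is needed is to name the group-by-time interaction as the treatment effect before analysis.

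Randomisation batch may be added as a covariate. Batches of 40 up to 122 patients give 40 + 40 + 40 + 2, so this costs 3 degrees of freedom, or 2 if the very small last batch is pooled with the one before it.

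The cost is one sentence of analysis wording. No extra patients, visits or measurements are needed, and the SPSS package already planned fits the model.

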## Pilot study

Participants for the pilot study were recruited from six weekly clinics in the Diabetes Centre, during the summer of 2006. Twelve eligible patients agreed to participate in the pilot and completed baseline assessment. Participants were divided into intervention and control groupss; six in the intervention and six in the control. Two participants in the intervention group, and one from the control group, withdrew from the study, leaving nine participants in the pilot study, four of which completed the intervention sessions. Pilot participants were not recalled for outcome assessment, since the small sample size would not allow for statistical analysis. A flow-chart of the recruitment process for the pilot study is shown in figure. 4 (Figure 4: Flowchart of recruitment of pilot participants).

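### The two-time-point repeated measures ANOVA is an unadjusted change-score comparison in returners; a baseline-adjusted comparison would be more precise and less exposed to arm-specific non-return

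*Protocol article*

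**What the plan says.** The Quantitative analysis section says that differences between the arms "will be analyzed for the two time-points (baseline and 6 months post- intervention" and then "Further statistical analysis will be based on repeated measures analysis of variance". No other test is named. The software sentence reads "SPSS Version 13.01 for Windows will be used in the analysis".

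The Sample size and rate of recruitment section takes HbA1c and well-being as primary outcomes: "a total sample size of 76 and 86 respectively, were calculated", for differences of 0.9% HbA1c and 3 points at 80% power. It raises the larger figure to "a final total number of 122 participants (61 in each group", a number that "is needed to ensure at least a 70% final response rate is met".

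Under Outcome assessment, 6-month values come from inviting both arms back to the clinic, so a value exists only for those who return. The article does not say in words how patients without a 6-month value are handled.

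**The concern.** With one follow-up visit, classical repeated measures ANOVA uses only patients with both values, and its group-by-time test compares mean change between the arms. Change depends on baseline: patients who start high tend to fall and patients who start low tend to rise, whatever the treatment. If returners in one arm differ from that arm's full baseline distribution and returners in the other arm do not, the change scores differ without any treatment effect.

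Such a difference between arms is possible here. Only the intervention arm has home sessions with a relative, a follow-up call and diaries over 24 weeks. Both primary outcomes would be affected. Even without bias, the unadjusted change score uses the baseline less efficiently than adjustment does.

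**Working it through.** **1. The plan's figure.** 86 / 0.70 = 122.9 in total, and 43 / 0.70 = 61.4 per arm. The stated 122 (61 per arm) agrees to within rounding. At 70% return, 0.70 × 122 = 85.4 patients have both values and 122 − 85.4 = 36.6, about 37, do not. The trial is therefore sized on patients with outcomes.

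**2. The test.** With two time points, the group-by-time F statistic is the square of the two-sample t statistic on change scores in patients with both values.

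**3. Inputs the article does not give.** No SD is stated. The 76 patients (38 per arm) and the 0.9 difference, at two-sided 5% (sidedness assumed) and 80% power, imply SD = 0.9 / [(1.960 + 0.842) × √(2/38)] = 1.40. If the 20% control improvement shrinks the difference to 0.72, the implied SD is 1.12 and the HbA1c biases below shrink by a fifth. The baseline to 6-month correlation r is assumed to be 0.3 to 0.7. Return is set at 70% in each arm, with a logistic dependence per SD.

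**4. Return depends on baseline in the intervention arm only, no true effect.** Expected change given baseline has slope (r − 1). If returners' mean baseline lies δ below that of their arm, the bias is (1 − r) × δ, positive meaning against the intervention. Solving the logistic model at 70% return gives δ = 0.141, 0.190 and 0.252 SD for odds ratios of 0.61, 0.50 and 0.37. Multiplied by 1.4, these are 0.20, 0.27 and 0.35 HbA1c points.

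| Odds ratio of return per SD | r = 0.3 | r = 0.5 | r = 0.7 |
|---|---|---|---|
| 0.61 | 0.14 | 0.10 | 0.06 |
| 0.50 | 0.19 | 0.13 | 0.08 |
| 0.37 | 0.25 | 0.18 | 0.11 |

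Simulation agrees: 0.18, 0.135 and 0.08 at 0.50, and 0.06 to 0.24 over the whole range. Against the 0.9 target that is 0.06/0.9 = 7% to 0.24/0.9 = 27%. Simulated two-sided type I error (r = 0.4 to 0.6) is about 6% at odds ratio 0.61 and 8 to 10% at 0.37. The excess lies on the side of apparent harm.

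**5. Same link in both arms.** The two shifts cancel. Simulated bias is 0.006 or less in size at every r.

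**6. What causes the bias.** In the one-arm scenario (odds ratio 0.50), complete-case ANCOVA on baseline drops exactly the same patients, yet its simulated bias is −0.006, 0.002 and −0.001. A likelihood contrast using all 122 baselines is also about 0. Conditioning on baseline is what removes the bias.

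**7. Precision, 43 per arm, r = 0.5.** Change score: 1.4 × √[2(1 − 0.5)] × √(2/43) = 0.30. ANCOVA: 1.4 × √(1 − 0.5²) × √(2/43) = 0.26.

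**8. Return depends on the unseen 6-month value, intervention arm only (odds ratio 0.50).** The change-score bias is close to −(1 − r) × 0.27 and the baseline-adjusted bias close to −(1 − r²) × 0.27. The second is larger by the factor 1 + r.

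| Simulated bias | r = 0.3 | r = 0.5 | r = 0.7 |
|---|---|---|---|
| Change score | −0.18 | −0.13 | −0.08 |
| Baseline-adjusted | −0.24 | −0.20 | −0.14 |

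Here both methods show a spurious benefit, and the adjusted one shows more.

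**The case against.** The strongest reply is that a journal article may leave missing outcomes, analysis populations and sensitivity analyses to an analysis plan that is not shown. The article never says that non-returners are dropped, and imputation could avoid it. The word that opens the ANOVA sentence also leaves some doubt whether it is the only primary test. This stands as far as missing-data handling goes, and its absence is not the point here. But repeated measures ANOVA is the only test the article names, and its group-by-time test remains an unadjusted change score however missing values are treated.

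Second, the bias is conditional. It vanishes when non-return works alike in both arms, and 30% is the largest loss planned for, not a forecast. At r = 0.5 the one-arm bias (0.10 to 0.18) is smaller than the standard error of 0.30. All of this stands.

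A reader might infer three stronger things that the document does not support:

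- **That losing non-returners is itself what biases the result, so that keeping all 122 baselines is the cure.** Complete-case ANCOVA loses the same patients and removes the baseline-driven bias equally well.
- **That the pilot shows differential loss.** It reports that "Two participants in the intervention group, and one from the control group, withdrew from the study", that is 2 of 6 and 1 of 6, but pilot patients were not recalled for outcome assessment. It says nothing about 6-month return or its link to baseline.
- **That a mixed model is unbiased whatever drives return.** Step 8 shows it can be worse than the stated method. Nor would adjustment for baseline HbA1c cover loss driven by weight or another variable outside the model. Larger biases can be produced by letting baseline act in opposite directions in the two arms, but nothing in the article suggests that pattern.

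**Conclusion.** The point holds as a weakness in the chosen method, not as a demonstrated bias. The stated test does not condition on baseline. It is therefore less precise than it could be, and open to bias if baseline predicts return differently in the two arms. For HbA1c that bias would be about 0.06 to 0.24 points against the intervention when higher baseline lowers return in that arm only. It would hide benefit rather than create it.

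The figures rest on an SD of 1.4, correlations of 0.3 to 0.7, odds ratios of 0.61 to 0.37 per SD and the full 30% loss. Only the 30% is stated in the article. Well-being was not simulated. The same reasoning applies to it, but its size would depend on its own SD, correlation and pattern of return.

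**What to change.** In the Quantitative analysis section, replace repeated measures ANOVA for HbA1c and well-being with a baseline-adjusted comparison of the 6-month value between the randomised arms. Either of two forms will do: ANCOVA on baseline, or a linear mixed model (SPSS MIXED) with a common baseline mean that includes all 122 patients.

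Add one sensitivity analysis that shifts the missing 6-month values in the intervention arm by stated amounts, for example up to 0.9% HbA1c and up to 3 well-being points, and reports where the conclusion changes.

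State the downside in the plan. Either model assumes that return depends only on observed data. If return in one arm depends on the unseen 6-month value, either can be more biased than the change score (about 0.14 to 0.24 against 0.08 to 0.18 points, towards a spurious benefit). That is why the shift analysis belongs with the change.

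The cost is a change of wording and a little more analysis work, with no new patients, visits or measurements.
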